**Methods:**

This study is a pragmatic randomized cluster trial. A total of 274 primary care centers will be randomized into two groups that will either maintain the current CHD risk detection strategy or add a screening program to detect asymptomatic PAD using ABI. In routine clinical practice, 10-year CHD and PAD risk are assessed using the Framingham-adapted (REGICOR) function and the REASON function, respectively. The study population will consist of patients aged 50 to 74 years with a CHD risk ≥ 7% and PAD risk ≥ 7%, making them candidates for an ABI measurement. Cases with an ABI result ≤ 0.9 will have their CHD reclassified as high or very high by doubling the initial REGICOR score and receive the recommendations of the lipid and cardiovascular risk guideline. The primary outcomes will be hard CHD, major adverse cardiovascular events (MACE), all-cause mortality, and improvement in CVD risk factors. Secondary outcomes include CHD (a composite of angina and hard CHD), cerebrovascular disease, and adverse effects from lipid-lowering medication. Survival analysis will estimate the effectiveness of adding the ABI screening strategy, with Cox models (intention-to-treat) and marginal structural models controlling for confounding variables.

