### Study design

2.1

This study will be conducted as a pragmatic cluster randomized trial in the primary care centers (PCC) of Catalonia. Patient monitoring will take place during a period of 2 years (2023–2025).

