### Sample size

2.3

The incidence of CV events (coronary or cerebrovascular disease, or symptomatic PAD) is expected to be 7% in the selected population during a period of 3 years. Accepting a 0.05 alpha risk and a 0.2 beta risk in a bilateral contrast, 20,171 people are needed in each arm, intervention and control groups, to detect a relative risk of 0.9.

Around 500.000 people aged 50–74 years have their CHD risk calculated in Catalonia per year. Out of those, we estimate that 36.000 will present both a REGICOR and REASON score ≥ 7%. Thus, in one and a half years we expect that there will be 54.000 people, 27.000 for each arm.

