### Statistical analysis

2.6

Quantitative continuous variables will be described with the mean and standard deviation or with the median and the interquartile range; categorical variables will be described with frequencies (%). Continuous variables will be compared using the Student’s t-test or Analysis of variance (ANOVA); Mann–Whitney U or Kruskal-Wallis will be applied when pertinent. Categorical variables will be compared using the Chi-squared or Fisher exact test as needed.

Survival analysis tests will be used to estimate the effectiveness of introducing a screening program using ABI. We will build classical Cox models and marginal structural models to account for confounding and intermediate variables. The reduction of the absolute risk and the number needed to treat (NNT) to prevent one additional event will also be calculated.

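### Centers are randomised, but the named analyses make no stated allowance for clustering by center, so standard errors would be too small and the type I error above 5%

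*Protocol article*

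**What the plan says.** The design is clear. Section 2.1 of the protocol article says: "This study will be conducted as a pragmatic cluster randomized trial in the primary care centers (PCC) of Catalonia". The abstract gives the unit and number: "A total of 274 primary care centers will be randomized into two groups".

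Section 2.6 sets out the analysis in two paragraphs. The first covers description and comparison of variables: Student's t-test or ANOVA for continuous variables, Mann-Whitney or Kruskal-Wallis as alternatives, and for the rest "Categorical variables will be compared using the Chi-squared or Fisher exact test as needed". The second covers effectiveness: "Survival analysis tests will be used to estimate the effectiveness of introducing a screening program using ABI. We will build classical Cox models". The same sentence goes on to name marginal structural models, and the purpose given for both is to deal with confounding and intermediate variables. Absolute risk reduction and NNT will also be calculated. The abstract repeats Cox (by intention to treat) and marginal structural models.

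Section 2.3 sizes the trial on a cardiovascular event rate that "is expected to be 7% in the selected population during a period of 3 years", "to detect a relative risk of 0.9", with this error specification: "Accepting a 0.05 alpha risk and a 0.2 beta risk in a bilateral contrast". The result is that "20,171 people are needed in each arm, intervention and control groups". The word cluster appears only where the design is described.

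**The concern.** Patients in one center share staff, workflow, catchment area and prescribing habits. The article itself points to such differences. Section 2.4.1 has each center define its own workflow around its workload and resources, and section 2.5.2 records provider quality standards and a deprivation index. Outcomes within a center are therefore likely to be correlated. Because the whole center is allocated to one arm, that correlation enters the variance of the treatment comparison in full.

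A Cox model with its standard variance, a t-test, a rank test and a chi-squared test all take patients as independent. Used in this design they count more information than the trial holds. The estimated effect is essentially unbiased, but its precision is overstated. This would affect hard CHD, MACE and all-cause mortality through the Cox models. It would also affect the risk-factor outcomes, which section 2.5.2 lists as primary, if the simple tests are used for them. No other group comparison is named that suits those variables.

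**Working it through.** **Step 1: does the plan's own sample size allow for clustering?**

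Inputs from section 2.3: p1 = 0.07, relative risk 0.9 so p2 = 0.063, two-sided alpha 0.05 (z = 1.960), power 0.80 (z = 0.8416). Mean proportion 0.0665, difference 0.007.

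Two-proportion formula for individual randomisation:

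n = [1.960 × √(2 × 0.0665 × 0.9335) + 0.8416 × √(0.07 × 0.93 + 0.063 × 0.937)]² / 0.007² = 19,887 per arm.

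With continuity correction:

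n' = (n/4) × [1 + √(1 + 4/(n × 0.007))]² = 20,171 per arm.

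This is the stated figure to the last digit, so the design effect built into the plan is 1. Sizing and named analyses both treat patients as independent.

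**Step 2: patients per center.**

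- At the stated requirement: 2 × 20,171 = 40,342; 40,342/274 = 147.2.
- At the recruitment forecast in section 2.3: 54,000/274 = 197.1.

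**Step 3: true size of a nominal 5% test that ignores clustering.**

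Design effect DE = 1 + (m − 1) × ICC, where m is the number of patients per center. The naive standard error is too small by the fraction 1 − 1/√DE. True two-sided size = 2 × [1 − Φ(1.96/√DE)].

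The documents give no ICC, so the values below are assumptions. Center sizes are taken as equal.

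| Assumed ICC | Patients per center | DE | SE too small by | True size |
|---|---|---|---|---|
| 0.001 | 147 | 1.15 | 6.6% | 6.7% |
| 0.005 | 147 | 1.73 | 24.0% | 13.6% |
| 0.01 | 147 | 2.46 | 36.3% | 21.2% |
| 0.001 | 197 | 1.20 | 8.6% | 7.3% |
| 0.005 | 197 | 1.98 | 28.9% | 16.4% |
| 0.01 | 197 | 2.96 | 41.9% | 25.5% |

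One line in full: at 197 per center and ICC 0.005, DE = 1 + 196.1 × 0.005 = 1.98, √DE = 1.407, 1.96/1.407 = 1.393, and 2 × [1 − Φ(1.393)] = 0.164.

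**Step 4: sensitivity to unequal centers.**

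With an assumed coefficient of variation of center size of 0.6, DE = 1 + [(1 + 0.6²) × m − 1] × ICC. At 54,000 people the three sizes become 8.2%, 20.0% and 30.6%.

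**Step 5: direction.**

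The size formula is symmetric. Under no effect, half of the false positives fall on each side: at ICC 0.01 and 197 per center, about 12.7% would show apparent benefit and about 12.7% apparent harm.

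**The case against.** The strongest reply is that this is a short statistics section in a journal article, and that the variance estimator belongs in the full protocol or SAP. The word classical most naturally sets ordinary Cox models against marginal structural models. A Cox model with center-clustered robust variance has the same hazard model and partial likelihood, so the sentence does not exclude it. That stands: a reader might infer that the plan rules out a cluster-adjusted analysis, and the text does not go that far. It does not remove the point, because the article names methods which, in their standard form, ignore clustering, gives them a purpose that is not within-center correlation, and rests on a sample size with a design effect of exactly 1.

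A second reply is that the t, rank and chi-squared tests may be descriptive. They follow the summary statistics, they include multi-group tests that two arms do not need, and section 2.5.2 refers to a bivariate analysis for finding confounders. This is fair. What remains is that the risk-factor outcomes are primary and no other suitable method is named for them.

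A third is that marginal structural models are often fitted with a robust variance. The article does not say so, and a robust variance at patient level would not cover clustering by center.

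Finally, the covariates listed in section 2.5.2, such as deprivation and provider quality, could absorb part of the between-center variation. That may lower the ICC, but it does not replace a clustered variance.

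**Conclusion.** The point holds. Centers are randomised, and the article states no allowance for this in the Cox models, the marginal structural models, the simple tests or the sample size. For any positive ICC, following the text gives intervals that are too narrow and a type I error above 5%.

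The direction is certain, but the size is not. The range from 6.7% to 25.5% in the table rests on assumed ICCs from 0.001 to 0.01, equal center sizes, a normal approximation, and the binary-outcome design effect carried over to the Cox comparison. Event outcomes may lie at the low end. Unequal centers would push the figures up and covariate adjustment may pull them down.

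Two stronger readings are not supported. A reader might infer a bias towards finding the screening programme effective. The test is two-sided and the excess is symmetric, so the fault is overstated precision in either direction. A reader might also assume much larger ICCs for the risk-factor outcomes and attach a correspondingly large error to all of them. The documents give no basis for such values, and glycated hemoglobin, which is measured only in patients with diabetes, has smaller clusters.

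This should be corrected before outcome data are analysed, because it bears on inference for the primary outcomes.

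**What to change.** State in section 2.6 that every effectiveness comparison allows for the center as the unit randomised:

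- **Cox models:** center-clustered robust variance or a center-level shared frailty, with one of them named as primary. Fixed center effects or stratification by center cannot be used, because arm does not vary within a center.
- **Marginal structural models:** variance clustered on center.
- **Risk-factor and binary outcomes:** linear or logistic mixed models, or GEE, with center as the cluster. Say that the t, rank, chi-squared and Fisher tests are descriptive only, if that is the intention.
- **Absolute risk reduction and NNT:** confidence intervals by a method that respects clustering. A bootstrap that resamples whole centers is one option.
- **Reporting:** give the assumed ICC and design effect, and report the observed ICC for each primary outcome.

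The cost is wording and code. No new data are needed, and 274 centers are enough for these methods. Confidence intervals will be wider, but valid. The sponsor should expect this to show in power. With 54,000 people and equal centers, a cluster-adjusted test of 7% against 6.3% has about 85%, 64% and 48% power at assumed ICCs of 0.001, 0.005 and 0.01, against 90% with no clustering. The corrected analysis does not cause that loss. The design already carries it, and an analysis that ignores centers would only hide it.

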### Ethical considerations

2.7

This study has received the ethical approval from the SIDIAP Scientific Committee and the Research Ethics Committee from the Institut d’Investigació en Atenció Primària Jordi Gol i Gurina (reference number 22/088-P). The researchers are committed to respect the principles of human experimentation and good medical research from the Declaration of Helsinki and the 17.2.d Spanish “Organic Law 3/2018, 5th of December, personal data protection, and digital rights guarantee.” The data for analysis will be sourced from pseudonymized electronic medical records and will only be available to the research team, which will sign a confidentiality agreement before obtaining them.

## Results and discussion

3

Cardiovascular diseases are the leading cause of death and disease burden worldwide. They have been associated with 6.2 million deaths in people aged 30 to 70 years in 2019 (19). The strategies to reduce this burden include the promotion of healthy lifestyles to improve behavioral risk factors and opportunistic screening in primary care facilities (20).

The introduction of this new PAD screening program using the ABI ≤ 0.9 predictive function will directly benefit the target population. The diagnosis of asymptomatic PAD at an early stage can be crucial for patient motivation and encourage acceptance of medical recommendations. This creates an opportunity to prevent disease progression, control risk factors, and improve lifestyles through smoking cessation, exercise, and diet.

The US Preventive Services Task Force stated that the available evidence is insufficient to establish population-based screening programs for PAD (20). However, this conclusion has been controversial because it did not consider the potential for preventing not only the progression of PAD itself, but also the development of severe CV events (17).

Moreover, a previous study, the Viborg Vascular Screening Trial (VIVA Study), evaluated the effectiveness of a combined screening strategy that included detection of PAD with ABI, detection of abdominal aneurysm, and blood pressure screening in men aged 65–74 years. After a 4.4-year follow-up, they observed a relative reduction in mortality of 7% in the intervention group, which translated into an absolute reduction of 0.6% (21). However, this study combines three interventions, which did not allow the evaluation of the screening with ABI alone. Besides, the study population included only men aged 65–74 without any criteria regarding CV risk. Another two ongoing trials also include ABI as part of their screening, but not in isolation (21, 22). The US Preventive Services Task Force does emphasize the need for conducting large trials to assess the effectiveness PAD screening using ABI measurement (20). These studies, in addition to isolating the effect of individual tests, should target individuals with an elevated risk of PAD who would not yet be receiving interventions to reduce their CHD risk (20). This is the population most likely to benefit from a screening intervention (20).

In our area, published evidence supports the effectiveness of preventive measures in individuals with asymptomatic PAD and no clinical CVD (23). In a previous study, we found that statin therapy was associated with a reduction in CV events and mortality in such a population, regardless of their CHD risk (23). The absolute reduction was comparable to that achieved in secondary prevention (23).

We expect that the impact of this intervention will not be limited to only CVD, but also other conditions related to lifestyle behaviors, such as reduction of smoking habits, increase in physical activity, and adhesion to Mediterranean diet. Importantly, the introduction of an ABI screening strategy into the current CHD risk assessment, is a groundbreaking approach to improve the CHD risk assessment. This innovative strategy is easy to perform and the technique included is non-invasive. Moreover, it aims to detect asymptomatic patients, thus becoming a useful risk modifier that will seek earlier interventions and overall improvement in health outcomes. This proposal offers a great opportunity, even more so since the COVID-19 pandemic has led to a reduction of CVD diagnoses at the primary care level. We expect that this strategy will contribute to restore and enhance CVD screening and prevention in the primary care settings (24).

### Limitations

3.1

A major challenge of this study could have been the implementation of the intervention, but this has been addressed beforehand. We conducted a detailed implementation pilot study with the support of a group specialized in this field. Another limitation could be the quality of the data. However, we expect to minimize this challenge using the EHR from the primary care information systems. These records have been used extensively in research and validated (25), including the validation of medication exposure, which will be confirmed through the billing records from the community pharmacies. We also acknowledge that the success of the results of this project will rely on participants’ adherence to the treatment and recommendations after being classified as high risk. Measures to address this limitation have been carefully implemented through training, the provision of educational materials, and the designation of appointed persons in each primary care center to raise awareness on PAD and its importance. Finally, extrapolation of results to a broader population or other demographic groups should be cautious. The aim of this study is to include the ABI measurement to refine the current CHD screening program of the population classified as medium CHD risk and aged 50–70 years old.
